### Clinical outcomes

#### Primary hypothesis

We hypothesize that the appropriately lagged post-intervention percentage of cases receiving unnecessary postoperative antibiotic prophylaxis will be significantly lower than in the pre-intervention period. To test this hypothesis, we will use an intention-to-treat approach for the primary analysis, including all complete case patient data from the NSQIP-P analysis set. A mixed-effects logistic interrupted time series (ITS) regression model will assess the impact of "order set change resulting in reduction" (1) versus "no order set change" (0) on prophylaxis prescriptions. The model will include the intervention (pre vs. post), time (in months), and an interaction term between time and intervention, including a random intercept to account for intra-hospital correlation in the model. The post-intervention slope (β_2) will be the primary estimate of interest (Fig. 2), but we will also investigate differences at 12, 24 and 36 months. The interruption point will be 12 months after each hospital’s first training, with sensitivity analyses at lags 9, 15, and 18 months as well. We will extend the model to adjust for age, surgical subspecialty, procedure type, hospitalization duration, and co-morbidities using Akaike information criterion (AIC)-based variable selection. Subgroup analyses by procedure type and hospital will also be conducted.

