**Fig. 2 Fig2:**
[figure not shown]
Illustrative example of the interrupted time series approach with estimated coefficients; $${\beta }_{0}$$ the trend prior to the intervention, $${\beta }_{1}$$ the immediate (local) effect following the intervention; $${\beta }_{2}$$ the post-intervention trend (target population measure)

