#### Power and sample size calculations

The sample size calculation is based on the primary outcome of the percentage of cases in which unnecessary postoperative antibiotic prophylaxis is administered among clean and clean-contaminated cases in the 20 participating hospitals. For the purposes of the power calculation, the staggered temporal implementation of the intervention in each of the hospitals is approximated by assuming a stepped-wedge cluster randomized trial design and adopting the sample size formula and associated web-based tool of Hemming and colleagues [35]. Utilizing data from our previous clinical trial specific to spine procedures [36], this sample size calculation depends on the targeted effect size (a percentage decrease from 45% measured in the pre-intervention period), the number of steps (10, with two hospitals implementing the intervention approximately every month over a period of 12 months), the estimated number of procedures per month (14 per hospital per month), and the intra-cluster correlation (ICC) coefficient (estimated at 0.12 from previous studies) [37]. With 20 hospitals implementing the intervention over a (1 [pre-] + 1 year [training] + 3 [post] =) 5 year study period, we envisage attaining at least 80% power to detect a difference in the pre- and post-intervention outcome measure of at least 5%, with a (two-sided) statistical significance level of 5% (and no missing data). Here we assume that existing surveillance measures capture data for the pre-intervention period and make the conservative assumption that all participating hospitals have one or more years pre-intervention surveillance data (not part of the study period), and *at least* 3 years post-intervention follow-up, allowing for the 12-month lag in post-training effect.

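### The primary estimate is the post-intervention slope, which is not the pre/post contrast that the hypothesis states and the power calculation assumes

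*Protocol article*

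**What the plan says.** All statements come from the protocol article's statistical analysis plan.

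- **Hypothesis** (Primary hypothesis): the "percentage of cases receiving unnecessary postoperative antibiotic prophylaxis will be significantly lower than in the pre-intervention period". This compares two levels.
- **Model** (same section): "The model will include the intervention (pre vs. post), time (in months), and an interaction term between time and intervention", with a random hospital intercept. The interruption is placed 12 months after each hospital's first training.
- **Primary estimate** (same section): "The post-intervention slope (β_2) will be the primary estimate of interest (Fig. 2". The sentence goes on: "but we will also investigate differences at 12, 24 and 36 months".
- **Fig. 2 caption**: β_0 is the trend before the intervention, β_1 is "the immediate (local) effect following the intervention", and β_2 is "the post-intervention trend (target population measure".
- **Power and sample size calculations**: at least 80% power "to detect a difference in the pre- and post-intervention outcome measure of at least 5" per cent, from a baseline of 45%, using a stepped-wedge approximation. This is again a level difference.

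**The concern.** The hypothesis and the power statement concern one quantity, and the primary estimate is another. A trend within the post-period says nothing by itself about whether the post-period is lower than the pre-period. It is zero when use drops at the interruption and stays down. It is negative when a decline that was already under way simply continues.

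The labels also disagree with the model. With intervention, time and their product, the product term is the change in slope, and the post-period trend is the sum of two coefficients. Two analysts following the text could report different primary results. What is at stake is the primary conclusion, in a design whose primary model has no untrained comparison hospitals.

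**Working it through.** **1. The plan's own figure.** Inputs from the power section: 20 hospitals, 10 steps of two hospitals, 14 cases per hospital-month, ICC 0.12, 45% to 40% (5% read as percentage points), two-sided 5%, 60 months. The standard stepped-wedge variance is

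Var = Nσ²(σ² + Tτ²) / [(NU − W)σ² + (U² + NTU − TW − NV)τ²],

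where U, W and V are the total, the squared period totals and the squared hospital totals of the exposure matrix. Here p̄(1 − p̄) = 0.425 × 0.575 = 0.2444, τ² = 0.12 × 0.2444 = 0.0293 and σ² = 0.88 × 0.2444 / 14 = 0.01536.

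- Steps spread over 12 months after a pre-year: U = 852, W = 16,232, V = 36,544, SE = 0.0206, z = 0.05 / 0.0206 = 2.43, power = Φ(2.43 − 1.96) = 68%.
- Steps every month: 60%. Eleven monthly periods only: 41%.
- Eleven equal periods over five years (14 × 60 / 11 ≈ 76 cases each): 98%.

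The stated 80% lies inside this range. The layout entered in the web tool is not given, so I draw no conclusion from the mismatch. What matters is that every version powers a single level shift, and none powers a slope.

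**2. What β_2 measures.** Write the model as logit p = hospital + b·t + c·post + d·t·post, with t counted from the interruption and post taken as the pre/post indicator.

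| Quantity | In the model |
|---|---|
| Pre-trend (Fig. 2, β_0) | b |
| Level change (Fig. 2, β_1) | c |
| Slope change (interaction) | d |
| Post-period trend (Fig. 2, β_2) | b + d |
| Difference from projected pre-trend at month k | c + k·d |

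A sustained step (b = d = 0, c < 0) gives β_2 = 0. A continuing decline with no effect (c = d = 0, b < 0) gives β_2 = b < 0.

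**3. Windows.** Post-interruption: 36 months (power section), 24 (the Clinical data section collects three years after the workshop, less the 12-month lag), 18 (data end in 2027; training during 2025 leaves 12 to 24 months, so 18 is the middle). Pre-interruption: 48 months (three baseline years plus the lag) or 24 (one baseline year plus the lag).

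**4. Sustained step, 45% to 40%.** The logit difference is ln(0.40/0.60) − ln(0.45/0.55) = −0.205. Information per month is 20 × 14 × 0.45 × 0.55 = 69.3. For n consecutive months, S(n) = n(n² − 1)/12, and

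Var(c + k·d) = [1/n₀ + ((n₀ + 1)/2 + k)²/S(n₀) + 1/n₁ + ((n₁ − 1)/2 − k)²/S(n₁)] / 69.3.

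| Pre/post months | Level change, k = 0: SE, z, power | 12-month contrast, k = 12: power |
|---|---|---|
| 48/36 | 0.0527, 3.89, 97% | 97% |
| 48/18 | 0.0648, 3.16, 88% | 93% |
| 24/36 | 0.0640, 3.20, 89% | 60% |

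The post-period trend and the slope change are both exactly zero here, so their tests reject at the nominal 5%. With both windows short (24/18), the level change has 79%.

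**5. Continuing decline, no effect.** The SE of the post-slope per year is 12/√(69.3 × S(n₁)). The trends are assumed. Near 45%, −0.05 and −0.10 logit per year are about 1.2 and 2.5 points per year (× 0.2475).

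| Post months | S(n₁) | SE per year | Rejection at −0.05 | Rejection at −0.10 |
|---|---|---|---|---|
| 36 | 3885 | 0.0231 | 58% | 99% |
| 24 | 1150 | 0.0425 | 22% | 65% |
| 18 | 484.5 | 0.0655 | 12% | 33% |

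The slope-change, level and 12-month tests stay at 5%.

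**6. Simulation check** (1,000 runs per scenario, hospital intercepts as fixed effects). For the step with 48/36 months, rejection is 4.5% for the post-slope, 4.7% for the slope change, 96% for the level change, and 94%, 80% and 58% for the 12-, 24- and 36-month contrasts. With no effect and a fall of 1 or 2 points per year, the post-slope signals a reduction in 39% or 91% of runs (48/36), and in 7.9% or 20.5% (48/18). With a drop from 45% to 35% and a rebound of 1 point per year (48/36), the post-slope is significant in the wrong direction in 43%.

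**The case against.** **β_2 may be the interaction.** The model has three terms and the caption has three coefficients. In the usual parameterisation the third is the slope change, so the caption may only be loosely worded. The figure is not shown, and a fuller analysis plan may exist. This stands in part: on that reading a linear secular trend is removed and the false-reduction problem goes. But the text and the caption agree on the other meaning, and the loss of power for a step remains at about 5% either way.

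**The level question is not ignored.** Differences at 12, 24 and 36 months will be examined, and β_1 is in the model. A reader might infer that a trial with a true lasting drop would be reported as a failure. The documents do not support that: the drop would be estimated and reported. What they support is that the primary test would not detect it. The listed differences are not primary, and it is not said whether they are taken against the projected pre-trend or the observed pre-level.

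**A trend may be what is expected.** A reader might also infer that a flat step is the likeliest effect. The documents do not say so. Teams choose different procedures, order-set changes are followed at 6, 12 and 18 months, and the Discussion names long-term trends and sustainability as a purpose. A gradual effect would show in the slope. I use the step because it is the effect the power calculation assumes.

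**Powering a simpler contrast is common.** True, and the approximation is disclosed. But it approximates a level shift, which is not the primary estimate.

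**Conclusion.** The point holds. As written, the primary estimate does not test the primary hypothesis, and the stated power does not belong to it. This should be settled before outcome data are analysed.

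The firm part is the missed effect: about 5% rejection for the step the trial was powered for, under either reading of β_2, against 88–97% for the level change in the three windows tabulated.

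The false-reduction part is conditional. A reader might infer that an existing decline would almost always be declared a success. That needs the literal reading of β_2, an assumed decline (the documents give no pre-trend) and a long post-period. The rates run from 12% to 99% across the cases shown, and drop to 5% for a linear trend if β_2 is the interaction.

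The calculations assume common linear logit trends, no random slopes and no calendar-period effects, so the absolute power figures are optimistic.

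**What to change.** 1. Name one primary contrast against the projected pre-trend at one stated month. An example is level change + 12 × slope change, which is the 12-month difference already listed with its reference made explicit. Give it a 95% confidence interval and a two-sided test.
2. Relabel the coefficients in the text and in Fig. 2 as pre-trend, level change and slope change. Report the raw post-intervention slope descriptively.
3. Base the power statement on the chosen contrast, with the pre- and post-interruption windows written out.

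A joint two-degree-of-freedom test of level and slope change would not do as the sole primary test. It has no direction, so it does not itself test for a lower percentage.

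The cost is a rewording of the Primary hypothesis section and the Fig. 2 caption, one linear combination from the model already planned, and a new power calculation. No new data are needed. The downside is that the power may look less favourable: for a 45% to 40% step and only 24 pre-interruption months, the 12-month contrast has about 60% (55% in simulation). The contrast also still relies on the pre-trend continuing in a straight line, which a design without a comparison group cannot verify.

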## Background

Antimicrobial-resistant (AMR) infections, driven by excessive and inappropriate antibiotic use, are an increasing public health emergency. A dramatic increase in the carriage of multidrug-resistant organisms has been observed since 2000 with projections indicating that if no efforts are made to improve antimicrobial use, AMR infections could result in 10 million deaths annually by 2050, surpassing the annual number of deaths due to cancer (8 million) [1–4]. *Clostridioides difficile* infection (CDI) is an adverse event associated with antibiotic use and is a more direct and immediate harmful outcome. Hospitalized children who develop CDI face an increased risk of death, prolonged hospitalization by up to seven days, and additional hospital costs of approximately $100,000 [5].

Even a single dose of perioperative antibiotic prophylaxis increases the risk six-fold for CDI [6, 7]. Studies indicate that inappropriate pre- and post-operative antibiotic prophylaxis occurs in up to 56% of cases, with unnecessary postoperative doses administered in 55% of low-risk procedures (clean and clean-contaminated cases) [6, 8, 9]. Improving the use of surgical antibiotic prophylaxis in the postoperative period across children’s hospitals presents a significant opportunity to reduce inappropriate antibiotic overuse. In published guidelines from the Centers for Disease Control and Prevention and the American Academy of Pediatrics Committee on Infectious Diseases, both strongly recommend limiting surgical antibiotic prophylaxis to a single perioperative dose for clean and clean-contaminated cases [10]. Furthermore, they advise discontinuing prophylaxis once the surgical incision is closed for uncomplicated procedures [11].

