##### Order sets review

To evaluate Behavior and Results domains of our evaluation model, an assessment will be conducted through 10-min structured interviews approximately 6-, 12-, and 18-months post-workshop training. An interview guide is provided in Supplementary File 2. Based on our experience from our Operatic 1.0 trial, this time interval is sufficient for ASPs to implement order set modifications across different surgical specialties, and participants are generally able to recall the work they have accomplished. The interview will inquire whether an order set modification was made, or a new order set developed (Yes/No, and number). For each impacted order set, we will inquire about the targeted procedure, the previous duration (no post-op antibiotics, 24 h or less, 25–48 h, or 48 h or more), and any changes in duration (eliminated, shortened, or no change). If the post-operative duration has been shortened, we will specify to what extent: no post-op antibiotics, 24 h or less, or 25–48 h. We anticipate some loss to follow-up due to staff turnover. In such cases, we will attempt to identify an alternative respondent, describe the study, and determine whether guideline integration through order set changes has continued.

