#### Clinical data

Clinical data will be gathered using the NSQIP-P database to assess overall impact on appropriate post-operative antibiotics prescribing and usage. De-identified, case-level clinical outcome data from NSQIP-P will be requested from each hospital shortly after participation in the workshop and subsequently on an annual basis until we have obtained three years of data post workshop participation. Each participating hospital adheres to the protocols and definitions outlined in the NSQIP-P Manual of Operations. Data abstraction at each site is performed by a full-time NSQIP-P data abstractor, typically a pediatric nurse with clinical expertise, who undergoes thorough training to ensure precise and reliable data collection. Data are gathered for 35 cases every 8 days at each hospital, contributing to a dataset of up to 1,500 cases annually. Since December 2018, antibiotic prophylaxis data for each case includes the type of antibiotic used, the timing of administration (within 1 h before incision), whether redosing occurred, and the duration of postoperative antibiotic use. Data collection continues for 30 days post-surgery to monitor for potential complications, such as SSI and CDI, which may appear up to a month after the procedure. Data elements include basic demographics (age, sex, date of procedure), type of procedure, wound class (clean, clean-contaminated, contaminated, or dirty), comorbidities, and resources utilized during surgery.

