#### Secondary hypotheses

We will also test multiple secondary hypotheses to assess the additional impact of the implementation strategy. These include: (1) the rate of SSI does not change post-intervention and (2) the rate of CDI decreases post-intervention. Analogous ITS-type statistical models will be fitted to investigate secondary outcomes. All estimated effects will be reported as odds ratios with 95% confidence intervals and p-values. The tests will be two-sided with a 5% statistical significance level and will be conducted using R statistical software.

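### The adjusted time-series model lists total hospitalization duration, a post-intervention variable, as a covariate, which can bias the adjusted antibiotic effect and possibly the SSI and CDI effects

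*Protocol article*

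**What the plan says.** Under Primary hypothesis, the protocol article first sets out a base model with no patient covariates: "The model will include the intervention (pre vs. post), time (in months), and an interaction term between time and intervention, including a random intercept" for hospital. The coefficient β2 "will be the primary estimate of interest (Fig. 2), but we will also investigate differences at 12, 24 and 36 months". The model is then extended to "adjust for age, surgical subspecialty, procedure type, hospitalization duration, and co-morbidities using Akaike information criterion (AIC)-based variable selection". Nothing limits the duration to the days before surgery.

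Three other places bear on the timing of that covariate:

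- Order sets review records, for each affected order set, "any changes in duration (eliminated, shortened, or no change"). The intervention therefore acts on the postoperative part of the stay.
- Background states that "Hospitalized children who develop CDI face an increased risk of death, prolonged hospitalization by up to seven days".
- Clinical data states that "Data collection continues for 30 days post-surgery to monitor for potential complications, such as SSI and CDI".

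For the secondary endpoints, Secondary hypotheses says only: "Analogous ITS-type statistical models will be fitted to investigate secondary outcomes". It lists no covariates.

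**The concern.** Age, subspecialty, procedure type and co-morbidities are settled by the time of the operation. Total stay is not. A changed order set can alter it, postoperative antibiotics can alter it, and on the protocol's own account CDI lengthens it. A variable that lies downstream of both the intervention and the outcome is not a confounder. Conditioning on it can move the intervention coefficient away from the effect of interest.

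For the antibiotic outcome, the adjusted estimate could understate a real reduction. For CDI, part of a real benefit could be hidden. For SSI, where the hypothesis is no change, a spurious increase could appear. A data-driven selection step would not remove the problem, because AIC rewards prediction and stay predicts all three outcomes.

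**Working it through.** **Inputs from the protocol.** The power section gives a 45% baseline, a 5-point target difference, 20 hospitals and 14 procedures per hospital per month. The study design gives 72 months (2022–2027). Background gives up to 7 extra days of stay with CDI. The other effects on stay and all its variances are assumptions, because the documents do not give them.

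**Planned effect.** log(0.40/0.60) − log(0.45/0.55) = −0.405 + 0.201 = −0.205, an odds ratio of 0.815.

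**Effect of adding stay.** Let Y be postoperative antibiotic use, μ(t) the mean stay at time t of cases without it, b the days that antibiotics add, and s the residual SD of stay (taken as normal). By Bayes' rule,

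logit P(Y=1 | t, stay) = logit P(Y=1 | t) + (b/s²)(stay − μ(t)) − b²/(2s²).

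At a fixed stay, the adjusted model therefore carries an extra −(b/s²)·μ(t). Whatever shape μ(t) has over time goes into the model term of the same shape. μ(t) excludes change in stay that passes through Y itself, so if the intervention alters stay only through antibiotic use there is no bias.

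**Which coefficient moves.** Take b = 1 and s = 2, so b/s² = 0.25, and a fall in stay of 0.5 day. The formula gives 0.25 × 0.5 = +0.125 in each row. The last column is a simulation of 400,000 cases per pattern with staggered interruptions, with slopes per 36 months.

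| Pattern of the fall in stay | Term that takes the +0.125 | Simulated, without → with stay |
|---|---|---|
| Linear over the whole period | Time | Time −0.008 → 0.115; interaction −0.218 → −0.214 |
| Step at the interruption | Level | Level up by about 0.12; interaction −0.190 → −0.189 |
| New slope from the interruption | Interaction | Interaction −0.169 → −0.059 |

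A step of −0.25 day would give 0.25 × 0.25 = +0.0625. If the 12-, 24- and 36-month differences are built from level plus slope, the step enters all three in full.

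**Check at the trial's size.** This run used 20 hospitals × 14 cases × 72 months = 20,160 cases, hospital intercepts and 60 simulated trials, with b = 0.5, s² = 2 and a slope change in stay of −0.5 day over 36 months. The formula predicts 0.5 × 0.5/2 = +0.125. With a true 36-month slope change of −0.204, the model without stay gave −0.198 and the model with stay gave −0.072, a shift of +0.126 (simulation SE 0.002). AIC kept stay in 60 of 60 trials.

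**Range for the antibiotic odds ratio.** With s² = 2, b from 0.25 to 1 day and a true odds ratio of 0.815, the affected contrast becomes:

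- no separate change in stay: 0.815
- 0.05-day fall: 0.820 to 0.835
- 0.25-day fall: 0.841 to 0.923
- 0.5-day fall: 0.867 to 1.046

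**SSI and CDI, if stay is adjusted for there too.** The odds ratio is multiplied by exp(b × fall/s²), with an assumed s² of 13.

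| Fall in stay | CDI, b = 7 (protocol's upper figure) | SSI, b = 4 (assumed) |
|---|---|---|
| 0.05 day | 1.03 | 1.02 |
| 0.25 day | 1.14 | 1.08 |
| 0.5 day | 1.31 | 1.17 |

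Stay is skewed in practice, so these are orders of magnitude.

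**The case against.** The strongest reply is that the base model, which carries the primary estimate, has no patient covariates; hospitalization duration enters only an extension. That stands. A reader might infer that the primary analysis as a whole is biased, and the document does not support this.

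A second reply is that the model contains time. A reader might infer that any fall in stay over 2022–2027 becomes bias in the intervention effect. It does not: a steady fall goes into the time coefficient. The exception depends on what β2 is. The text of Primary hypothesis has an interaction term, but the caption of Fig. 2 labels β2 as the trend after the intervention. Read as that total trend, β2 would take in a smooth decline directly.

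Third, +0.125 is about 60% of −0.205 (0.125/0.205), and a reader might apply that percentage to β2. For a step change in stay it belongs to the level term and the dated contrasts. Biasing an interaction β2 requires stay to change slope at each hospital's interruption by a route other than antibiotic use, and the documents give no evidence of such a break.

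Fourth, the use of stay in the SSI and CDI models is inferred from the word analogous, and some events within the 30-day window follow discharge. Both points stand. Stay would still be a post-intervention variable, and for these outcomes a route is plausible: fewer postoperative antibiotics may shorten stay without passing through SSI or CDI.

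Finally, stay may be meant as a proxy for severity. Procedure type and co-morbidities already describe severity before the outcome, and preoperative stay could do so without this problem. It is also tempting to add that AIC will discard needed case-mix variables, or that leaving out wound class causes bias. Neither is shown: with roughly 20,000 cases AIC drops only covariates that add almost nothing, and the sample size section already restricts the outcome to clean and clean-contaminated cases.

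**Conclusion.** The concern holds for the adjusted model. Listing total hospitalization duration as a candidate covariate conditions on a variable that the intervention and the outcomes can change, and AIC would be expected to keep it. The unadjusted model is not touched.

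Bias is possible, not certain. It is nil if stay changes only through the modelled outcome, small for a separate change of about 0.05 day, and material for changes of 0.25 to 0.5 day. Which estimate is affected depends on the pattern: the level term and dated contrasts for a step, the interaction for a change of slope, and the time term for a linear trend. All sizes rest on assumed effects and variances of stay, apart from the protocol's upper figure of seven days for CDI. The SSI and CDI part is conditional on those models using the same covariates.

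**What to change.** Delete hospitalization duration from the covariates of the adjusted antibiotic model and of any adjusted SSI or CDI model. If a marker of severity before surgery is wanted, use preoperative stay, provided the database holds it.

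As a suggestion only, keep a prespecified set of baseline covariates (age, procedure type or subspecialty, co-morbidities, optionally wound class) rather than choosing them by AIC. Reported intervals and p-values would then need no allowance for selection.

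The cost is one sentence of text and slightly less explained variation in the adjusted model. Deleting the covariate needs no new data.
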